Eligibility criteria for the participants are presented in Table 1. A nutritionist will perform the intervention. The participants will be randomized into three equal groups using a blocking stratified sampling method by age and sex to ensure equal numbers within each age and sex strata using a computerized table of random digits. The groups are probiotic, synbiotic (6 grams inulin + probiotic) or placebo (maltodextrin) consumers for 6 months. The appearance and packaging of the three products are identical. Details about the content and preparation process of pruductes will be presented in section 3.2. The inulin dose of 6 g/d as the prebiotic in the synbiotic type was selected based on previous studies [22]. This dose was suggested and tested to be well-tolerated. Participants, laboratory staff, and investigators will be blinded to the allocation of probiotic, synbiotic or placebo, which will be conducted by the study pharmacist (who will then dispense blinded supplements or placebo to the investigators). The subjects will be instructed to dilute the powder in water and to drink it after their main meal to minimize the killing of the probiotic by gastric acid. Due to the dietary-controlled nature of the study, water was selected as the beverage for the delivery of supplements. Individuals will be appropriately blinded in performing outcome measurements and type of supplement. The supplements will be assigned letter A, B or C and are otherwise identical. All of the participants have been counseled to follow an energy-balanced diet and physical activity recommendations 6 months previous to start of the study. They will be advised not to modify their daily dietary and physical activity habits. To ensure that these habits have not been modified during the experiment, the participants will be instructed to record daily food and physical activity diaries, which will be checked monthly during face-to-face visits by a dietitian. Also, the participants will be advised not to modify their medication during the experiment. During these visits, the researchers will check the compliance with the study supplementation and the development of any adverse events. Compliance will be assessed based on returned tablet counts. The project coordinator will assess and manage solicited and spontaneously reported adverse events of trial interventions.

**Table 1 Tab1:** Eligibility criteria for the effects of probiotic or synbiotic supplementation on metabolic syndrome indices

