### Statistical analysis

Record data including outcome data and adverse events will be double-entered on SPSS software (Version [15], SPSS Inc., Chicago, IL, USA) to secure its validity. Descriptive univariate analyses on all study variables through presenting them as mean ± standard deviation (SD) (for normally distributed continuous) or median [interquartile range (IQR)] for nonnormal quantitative data and frequency (percentage) for categorical data will be conducted. Data will be evaluated for the presence of outliers, violations of normality, and missing data. Major violations of normality will be corrected with an appropriate transformation procedure, i.e., logarithmic transformation for positively skewed and exponential function for negatively skewed data. In the case of an outlier, rather than transform the data, the outlier will be “Winsorized,” that is, replaced by the most extreme value in the tail of the distribution as well as a sensitivity analysis being performed when outliers are in or out of analyses. To test our hypothesis that probiotic and synbiotic supplementations will improve main outcomes in prediabetic participants, a repeated measures analysis of variance (ANOVA) with a between-subject factors approach will be used. The multiple observations will be considered as nested data within individuals. This will allow us to make inference about time effects (i.e., comparison between the time points while accounting for the correlation in the data) in each studied treatment group and to make inference about differences between competing treatment groups. This approach enables us to make an inference regarding the group by time interaction as a primary important interested component. As a perquisite, the assumption of sphericity will be evaluated using a Muchly test, in the case of violation, multivariate or Huynh-Feldt approaches will be employed. A compound symmetry error structure will be chosen for this model when the assumption is present. We will use repeated measures ANOVA as the main approach for testing all our hypothesis regarding the main outcomes; simultaneously, independent *t* test along with Bonferroni adjustment will be conducted for comparing outcomes in each follow-up time point between study groups. Some prespecified subgroup analysis will be done based on some confounding variables such as age, gender, etc., for detecting significant differences in intervention efficacy across the strata of mentioned variables. However, these subsamples will be compared to the main dependent variables at baseline. If the groups are found to be different from one another then they will be entered into the model as a covariate. On the other hand, the baseline values of the main dependent variables and other potential confounding variables will be considered as covariates and they will be adjusted in all fitted models. The study analyst will have access to the results and final trial dataset and make the final decision on interim analyses and terminate the trial if there is any harm for the participants.

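### Two covariate rules stand side by side, so it is unclear whether the stratification factors age and sex are in the primary model

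*Protocol article*

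**What the plan says.** The Overview in Methods/Design states that participants will be "randomized into three equal groups using a blocking stratified sampling method by age and sex".

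The Statistical analysis section names the primary method: "We will use repeated measures ANOVA as the main approach for testing all our hypothesis regarding the main outcomes". On covariates it then says, in this order:

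- "Some prespecified subgroup analysis will be done based on some confounding variables such as age, gender, etc";
- the subgroups formed in this way are to be checked against each other on the main outcomes before treatment starts;
- "If the groups are found to be different from one another then they will be entered into the model as a covariate";
- "the baseline values of the main dependent variables and other potential confounding variables will be considered as covariates", followed by "they will be adjusted in all fitted models".

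The section does not say which variables the last rule covers. No sentence names age and sex, as randomisation strata, as terms of the primary model. The number of age strata is not given either.

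**The concern.** The third item is conditional: a variable enters if a comparison at baseline shows a difference. The fourth is unconditional. Age and gender fit both, because the first item calls them confounding variables. Two analysts could fit different primary models and each claim to have followed the protocol.

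The conditional rule is also a poor way to choose covariates. It asks whether age or sex subgroups differ on the baseline outcome. The baseline outcome is already in every model, so a further covariate helps only through what it says about follow-up beyond baseline, and the rule does not look at that. Factors used to stratify randomisation should be in the model because the design used them. Stratification removes their chance imbalance from the treatment comparison. A model that omits them still counts their variation as residual error, so it reports a standard error larger than the true one.

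At stake are an undetermined primary model and, in some circumstances, a conservative test.

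**Working it through.** The plan gives no figure on this point and no age or sex effect, so those effects are assumed below, in SD units per factor.

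**Inputs from the protocol.** 40 per group in three equal groups; one baseline and two follow-up observations (v = 1, w = 2); ρ = 0.7; two-sided α = 0.05; Δ = 0.60 (all from Sample size and Overview). Whether the stated group size follows from the plan's formula is a separate matter and is not used here.

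**Residual variance after baseline adjustment.** The plan's own factor is R = (1 + 0.7)/2 − 0.7² = 0.85 − 0.49 = 0.36. With 40 per group, the true SE of a pairwise difference is √(2 × 0.36/40) = 0.134.

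**Omitting two balanced two-level factors.** A factor that shifts follow-up by g beyond baseline adds g²/4 to the residual variance, so two add g²/2. The model SE is then too large by √[(0.36 + g²/2)/0.36].

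- g = 0.3: √(0.405/0.36) = 1.061. The effective critical value is 1.96 × 1.061 = 2.08, and the two-sided type I error is about 0.038.
- g = 0.5: √(0.485/0.36) = 1.161. The critical value is 2.27, and the type I error is about 0.023.

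**Simulation.** Three arms of 40, four balanced age-by-sex strata, analysis of covariance on the mean of two follow-up values, 4,000 runs per scenario, treatment effect 0.35 SD for power. The rule enters each factor if its baseline t test gives p < 0.05.

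| Age/sex effect per factor | Power, always in | Power, rule | Type I, always in | Type I, rule |
|---|---|---|---|---|
| Same at baseline and follow-up, 0 to 0.8 | 0.72–0.74 | 0.72–0.74 | 0.049–0.055 | 0.048–0.055 |
| 0.3 beyond baseline | 0.73–0.74 | 0.69 | 0.046–0.048 | 0.034–0.037 |
| 0.5 beyond baseline | 0.72 | 0.61 | 0.050 | 0.026 |

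The Monte Carlo error of a 0.05 rate is √(0.05 × 0.95/4000) = 0.003, so the upper values near 0.055 are not evidence of inflation. The empirical SE of the estimate is 0.132 to 0.137 under both approaches, in line with 0.134.

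**Why the first row shows no loss.** A factor with equal effect g at baseline and follow-up leaves only (1 − 0.7)g after baseline adjustment. For g = 0.5 that is 0.15 per factor, and the SE inflation on omission is √[(0.36 + 0.15²/2)/0.36] = 1.016. A factor acting on follow-up only through baseline leaves nothing.

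**How the test behaves.** With 60 against 60 (an assumed even split), a baseline shift of 0.2, 0.3 or 0.4 SD reaches p < 0.05 in 19%, 37% or 58% of trials. So for moderate factors, entry depends largely on chance. Where a factor affects follow-up but not baseline, it enters only at the 5% false-positive rate. That is where omission costs most.

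**At the plan's own effect size.** At Δ = 0.60 with 40 per group, 0.60/0.134 = 4.47. Power is Φ(4.47 − 1.96) = 0.994 with the factors in and Φ(4.47 − 2.27) = 0.986 with both omitted at g = 0.5, so the loss is under one point. The larger losses in the table belong to a treatment effect of 0.35 SD.

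**The case against.** A reader might infer that age and sex enter only if a baseline test is positive. The text does not support that. The next sentence adjusts for other potential confounders in all fitted models, and age and gender have just been called confounding variables. Always adjusting for them is a natural reading. It does not settle the matter, however: if they are always in, the conditional sentence has no purpose.

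The conditional sentence also follows directly on the subgroup sentence, so its model may be the subgroup model alone, and what its pronouns refer to is unclear. This is a fair point. It makes the text ambiguous rather than sound.

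A reader might take the rule for the familiar test of imbalance between treatment arms. As written, it compares age and sex subsamples on the baseline outcome, so the standard criticism of such imbalance tests does not carry over directly. Nor can this comparison steer the model towards a favoured arm, since it uses no treatment effect and the Randomization section blinds the data analysts.

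Finally, a reader might infer that the precision gained by stratification is thrown away. It is not: the estimate keeps the balance, as the near-identical empirical SEs show. What can suffer is the reported SE.

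A full covariate list may properly sit in an analysis plan that is not shown. The point here is narrower: the protocol states a rule, and the next sentence is hard to reconcile with it.

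**Conclusion.** The concern holds as an unresolved conflict between two stated covariate rules. The protocol does not settle whether the stratification factors are in the primary model, and on one reading a preliminary baseline test decides. It cannot be said that the primary model omits them.

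The consequence runs from nothing to moderate. Under the conditional rule the simulated power loss is between about 0 and 11 points (0.72 against 0.61 at worst), and the test becomes conservative, with type I error down to about 0.026. There is no inflation of type I error.

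The figures rest on assumed age and sex effects of up to 0.5 SD per factor beyond baseline, two levels per factor, evenly filled strata, and a treatment effect of 0.35 SD. They concern the group difference averaged over two follow-up values. The group-by-time interaction, which the plan also stresses, was not simulated. There, a factor with a constant effect over time cancels from within-person contrasts, so omission would matter only if its effect changes with time.

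**What to change.** Delete the sentence that makes covariate entry depend on a baseline difference. State that the primary repeated measures model always includes the baseline value of the outcome, the age stratum and the sex used at randomisation, whatever the baseline data show. Define the age strata. Describe the subgroup analyses separately, as tests of interaction between treatment and the subgroup variable, with no bearing on the covariates of the primary model. If other confounders are to be adjusted for, name them in advance.

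The change takes a sentence or two and needs no extra data. It uses a few degrees of freedom; the exact number depends on how many age strata there are, which the document does not give. In the simulations, always including both factors cost no visible power even when they had no effect (0.741 with or without them).

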
### Treatment of missing data

Missing data are common in longitudinal studies. Based on patterns and the mechanism of missing data, an appropriate multiple imputation approach will be followed for completing missing data. We will use an intention-to-treat analysis as our primary analytic approach. As an alternative statistical analysis method using linear mixed model ANOVAs or generalized estimating equation (GEE) for longitudinal analysis, we will compare main study outcomes across the treatment groups. Through employing these methods, the possibility for using all available data to construct weighted averages across the different patterns of missing data to provide valid point estimates, and confidence intervals for population parameters will be provided [28]. As a secondary analysis, we will conduct a per protocol analysis and restrict the analyses to only those individuals who complete the intervention; if the results differ we will interpret the findings based on the intention-to-treat analysis.

## Discussion

Up to now, the therapeutic effects of gut microbiota manipulation, through the administration of probiotics/prebiotics/synbiotics, have been discussed, but there is little information regarding if they improve metabolic indicators in humans. In addition, the potential benefits of these biopharmaceuticals in prediabetic individuals who are at high risk for developing type 2 diabetes and experiencing cardiovascular events has received little attention. This trial will address this important research gap, by exploring and comparing the role of probiotics and synbiotics in modifying anthropometric, glycemic, and lipid profiles among prediabetic individuals.

The innovative aspects of this clinical trial include: (1) testing hypotheses involving a novel concept for which there are little strong data in humans; (2) focusing on individuals at high risk for T2DM, including those with prediabetes; (3) carrying out a synthesis and study of synbiotics for the first time in Iran; (4) following up the participants for 1 year after the intervention phase; and (5) comparing the effects of probiotics and synbiotics.

Importantly, our findings could have a significant impact on clinical practice and public health as a simple and efficacious adjunctive approach for prevention or management of T2DM if our hypotheses are supported. The primary challenge of our study will be participant adhesion and retention. This challenge will be managed by the project coordinator who will have weekly contact with participants in which any concerns or issues will be immediately addressed.

If these supplements are shown to be effective in management of prediabetes and preventing diabetes, they would be a very attractive alternative or adjunctive for current medications.

### Trial status

Estimated enrollment is 120 participants.

The study start date was June 2016, and estimated study completion date is June 2018.

## Abbreviations

ANOVA: Analysis of variance
BMI: Body mass index
CVD: Cardiovascular disease
HbA1c: Glycosylated hemoglobin
HDL: High-density lipoprotein
HOMA-B: Homeostatic model assessment of beta-cell function
HOMA-IR: Homeostatic model assessment of insulin resistance
LDL: Low-density lipoprotein
qPCR: Quantitative real-time polymerase chain reaction
T2DM: Type 2 diabetes mellitus
WHR: Waist-to-hip ratio
